#### Secondary efficacy analysis

Qualitative evaluation of the image quality of the coronary artery will be performed. Two experienced observers will review all coronary CT images and score the image quality for each segment with a 4-point grading system on visual assessment: Grade 1, nondiagnostic; Grade 2, reduced image quality; Grade 3, nonlimiting artifacts; and Grade 4, complete absence of motion artifacts with good attenuation of the vessel lumen and clear delineation of the vessel walls with the additional ability to assess luminal stenosis.

Quantitative evaluation of image quality of perfusion CT will be performed. The myocardium will be divided into 16 segments according to AHA classification, and the HU value of each segment will be measured. Mean HU value, SNR, and CNR of myocardial enhancement will be compared between the different arms of the trial.

Diagnostic accuracy of coronary CT angiography compared to invasive coronary angiography will be calculated. Segment-basis analysis, sensitivity, specificity, positive predictive value, negative predictive value, and accuracy of CT angiography for diagnosis of the presence of CAD defined by more than 50 % diameter stenosis compared to invasive coronary angiography will be calculated and compared between the different concentrations of contrast agent by means of a generalized estimating equation based on a binary logistic model.

Quantitative evaluation of image quality of coronary artery will be performed on a per-vessel and per-segment basis.

### Statistical methods

#### Sample size and power calculation

The noninferiority margin was justified by an indirect confidence interval approach using the point estimate because the constancy assumption was not applicable in this trial. In a previous study [11], the reduction rate between iopamidol 370 mgI/ml and iodixanol 320 mgI/ml was 18 % (from 439.96 to 362.06 HU), and we assumed that the HU value between the low-concentration and high-concentration groups would be the same. Consequently, we estimate 9 % (0.5 × (18 % - 0 %)) of the reported mean HU [10] to be the noninferiority margin, allowing a loss of less than 50 % of the active control effect, which corresponds to a noninferiority margin of 51.26 HU [12]. Clinically, 250–300 HU is considered sufficient enhancement for coronary angiography [13]. Therefore, a reduction of 51.26 HU from 439.96 HU, which results in 388.7 HU, is clinically acceptable. For the mean contrast enhancement as an attenuation value of CT (HU) in the noninferiority test, we assumed same mean HU among the three groups and a standard deviation of 118.93 for the HU based on a previous study [10]. With these assumptions and a 10 % dropout rate, 106 subjects per group are needed to obtain 80 % statistical power with a corrected two-sided α ≒ 0.0167 (=0.05/3).

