**Methods/Design:**

The CONCENTRATE study is a prospective, multicenter, noninferiority, randomized trial evaluating the enhancement effect of low-concentration contrast agents (270 and 320 mg iodine/ml) compared with a high-concentration contrast agent (370 mg iodine/ml) in the coronary artery and myocardium of coronary artery CT angiography. The primary efficacy measurement is the enhancement of coronary arteries as measured in Hounsfield units. The target population comprises 318 patients with suspected coronary artery disease who have been referred for clinically indicated nonemergent coronary CT angiography. Eligible participants are randomized for three different concentrations of the contrast agent in a 1:1:1 allocation ratio to one of three arms. The CONCENTRATE trial is a double-blind study, where the subjects and the outcome assessor are blinded to the concentration of the contrast agent used for coronary the CT angiography. Eight clinical sites in Korea are participating in this trial.

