#### Primary statistical analysis

Per-protocol analysis will be performed primarily; an additional intention-to-treat analysis will be also performed. The 98.33 % confidence interval (CI) for the difference of mean contrast enhancement in the ROIs will be calculated. The noninferiority of the low-dose group compared to the high-dose group will be demonstrated if the lower bound of the two-sided 98.33 % CI lies above the pre-specified noninferiority margin. Because missing values are expected for 5 % or fewer of the participants, we have planned complete-case analysis for the primary analysis. To account for multiple observations per patient in secondary analysis, we will use a linear mixed model, including fixed effects for the group and random intercepts for the patient. Patients with a missing observation in some vessel or segment will be included in the per-vessel and per-segment analysis by using the linear mixed model. Analysis of covariance (ANCOVA) with BMI as a covariate will be used to compare the mean HU of the myocardium on static perfusion CT. Inter-reader agreement for the assessment of image quality will be evaluated using a linearly weighted kappa statistic. Analysis of variance (ANOVA) will be used to compare mean changes in heart rate before and after CT examinations among the three groups. To compare the diagnostic accuracy of invasive coronary angiography for diagnosis of significant coronary artery stenosis with more than 50 % stenosis among the three groups, logistic regression analysis using a generalized estimating equation (GEE) will be used to account for the correlation among multiple segments within the same subject. All statistical analyses will be performed using SAS (SAS Ver. 9.2; SAS Institute, Cary, NC, USA) and two-sided *P* values less than 0.05 will be considered statistically significant.

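### The 106 per group was sized on a one-sided 0.0167, but the protocol states and tests a two-sided 0.0167, so power per comparison is about 72%, not 80%

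*Protocol article*

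**What the plan says.** The protocol article, under *Sample size and power calculation*, gives the design target as "80 % statistical power" with a "corrected two-sided α ≒ 0.0167 (=0.05/3"), and concludes that "106 subjects per group are needed to obtain" it. The inputs there are equal mean HU in the three groups, an SD of 118.93 HU, a 10% dropout rate, and a reduction that "corresponds to a noninferiority margin of 51.26 HU". Three groups of 106 make up the 318 patients given in the abstract.

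Under *Primary statistical analysis* the decision rule uses the same level: noninferiority is shown "if the lower bound of the two-sided 98.33 % CI lies above the pre-specified noninferiority margin". That analysis is per-protocol with complete cases.

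**The concern.** A noninferiority decision uses only one end of the interval. A two-sided 98.33% interval leaves 0.0167/2 = 0.0083 in the tail that decides, so the planned rule is a one-sided test at 0.0083. If the sample size was computed with the full 0.0167 in one tail, the size and the test use different error rates, and the stated power does not belong to the planned analysis.

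In a noninferiority trial, missing power means that protocols which really are equivalent fail to be shown so. A failed comparison would also be read against a power of 80% that the design did not have.

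**Working it through.** **Inputs** (all from *Sample size and power calculation*): margin 51.26 HU, SD 118.93 HU, true difference 0, power 80% (z = 0.8416), dropout 10%.

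**Formula**, evaluable patients per group for comparing two means: n = 2 × (SD/margin)² × (z_α + 0.8416)². Here 2 × (118.93/51.26)² = 10.766. Enrolled = n/0.9.

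**Step 1: the protocol's own figure, and the figure its stated alpha needs**

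| Alpha | z_α | Evaluable | Enrolled |
|---|---|---|---|
| One-sided 0.0167 (stated nowhere) | 2.128 | 94.9, so 95 | 105.6, so **106** |
| Two-sided 0.0167 (stated and analysed) | 2.394 | 112.7, so 113 | 125.6, so **126** |

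The one-sided 0.0167 gives the protocol's figure exactly. The noncentral t version gives 97 evaluable and 108 enrolled for the first row, and 115 and 128 for the second. Other one-sided levels with the stated 10% dropout do not explain 106: 0.025 gives 95 enrolled and 0.0125 gives 115. A one-sided 0.0125 with no dropout (103) or 5% dropout (109) comes near, but contradicts both the stated dropout and the division of 0.05 by 3.

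**Step 2: power of the planned rule at the planned size**

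SE = 118.93 × √(2/n); power = Φ(51.26/SE − 2.394).

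| Evaluable per group | SE (HU) | 51.26/SE | Power per comparison |
|---|---|---|---|
| 95 (10% lost) | 17.26 | 2.971 | **71.8%** (t: 71.0%) |
| 101 (about 5% lost) | 16.74 | 3.063 | 74.8% (t: 74.1%) |
| 106 (none lost) | 16.34 | 3.138 | **77.2%** (t: 76.5%) |

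For contrast, 95 evaluable with z_α = 2.128 gives Φ(2.971 − 2.128) = 80.0%, which is the stated power under the level actually used for sizing.

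**Step 3: the shortfall in patients**

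126 − 106 = 20 per group, or 60 in total (378 against 318).

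**Step 4: both low-concentration arms**

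The two comparisons share the 370 mgI/ml arm, so with equal group sizes their test statistics correlate at 0.5. At 95 evaluable, the chance that both pass is 57.9% under the 98.33% interval. It would be 68.7% with a one-sided 0.0167, so only about 11 points of the distance below 80% come from the alpha mismatch. The rest comes from requiring two successes.

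**The case against.** - **The error is on the safe side.** This stands. The rule tests at one-sided 0.0083, so false claims of noninferiority are not inflated and a positive result remains valid. What is wrong is the stated power.
- **The 72% is the pessimistic end.** The analysis section expects missing values in 5% of participants or fewer, and at that loss power is about 75%. This stands in part: 72% to 77% is the fair range. But 10% is the protocol's own design figure, a per-protocol set can lose patients for reasons other than missing data, and even zero loss does not give 80%.
- **The word two-sided may be a slip.** This does not stand. The analysis section independently specifies a two-sided 98.33% interval. A one-sided 0.0167 would correspond to a 96.67% interval, which appears nowhere. A separate analysis plan could not settle this quietly: one that follows the stated rule keeps the 72%, and one that uses a 96.67% interval contradicts the protocol.
- **The protocol never promises 80% for both arms jointly.** This stands, so the 58% should be read against 69% and not against 80%.

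**Conclusion.** The concern holds. The sample size, the stated two-sided alpha and the stated power cannot all be true. Under the rule the protocol specifies, 106 enrolled per group give 71.8% power per comparison with the planned 10% dropout and 77.2% with none. With the planned dropout, a truly equivalent low-concentration protocol fails in about 28% of trials instead of 20%. These figures take the protocol's margin, SD and equal means as given, and use a two-group comparison of means with the normal approximation. The t distribution lowers each power by less than one percentage point.

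**What to change.** Correct the power sentence: with 106 enrolled per group and the two-sided 98.33% interval, power is about 72% per comparison after 10% dropout and about 77% with no dropout. State for each alpha whether it is one-sided or two-sided, in the protocol and in the analysis plan. This costs one corrected sentence and no patients, and the stated power becomes less favourable.

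If the 80% is to be kept, there are two ways:

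- **Enrol more.** 126 per group, 378 in total, which is 60 more patients.
- **Change the test.** The noninferiority objective involves only two comparisons with the 370 mgI/ml arm. Holm's procedure over those two, at an overall one-sided 0.025, gives 81.6% per comparison and 74% for both at 95 evaluable. It needs no more patients, but it replaces the division by 3 and the 98.33% rule. That is a change to the primary decision rule in a trial that has been recruiting since July 2015, so it would need a documented amendment made before any results by arm are seen.

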#### Primary statistical analysis

Per-protocol analysis will be performed primarily; an additional intention-to-treat analysis will be also performed. The 98.33 % confidence interval (CI) for the difference of mean contrast enhancement in the ROIs will be calculated. The noninferiority of the low-dose group compared to the high-dose group will be demonstrated if the lower bound of the two-sided 98.33 % CI lies above the pre-specified noninferiority margin. Because missing values are expected for 5 % or fewer of the participants, we have planned complete-case analysis for the primary analysis. To account for multiple observations per patient in secondary analysis, we will use a linear mixed model, including fixed effects for the group and random intercepts for the patient. Patients with a missing observation in some vessel or segment will be included in the per-vessel and per-segment analysis by using the linear mixed model. Analysis of covariance (ANCOVA) with BMI as a covariate will be used to compare the mean HU of the myocardium on static perfusion CT. Inter-reader agreement for the assessment of image quality will be evaluated using a linearly weighted kappa statistic. Analysis of variance (ANOVA) will be used to compare mean changes in heart rate before and after CT examinations among the three groups. To compare the diagnostic accuracy of invasive coronary angiography for diagnosis of significant coronary artery stenosis with more than 50 % stenosis among the three groups, logistic regression analysis using a generalized estimating equation (GEE) will be used to account for the correlation among multiple segments within the same subject. All statistical analyses will be performed using SAS (SAS Ver. 9.2; SAS Institute, Cary, NC, USA) and two-sided *P* values less than 0.05 will be considered statistically significant.

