### Randomization

All enrolled subjects are randomly assigned to one of three concentrations of contrast agent in a 1:1:1 ratio based on each trial site. We use concealed allocation and an adequate computer-generated allocation sequence to avoid selection bias. Thus, neither the patient nor the outcome assessor knows to which group the patient is allocated. Therefore, if unblinding is deemed necessary, any of the investigators, coordinators, or CT operators can provide the information of the contrast agent used. If the assessors of the outcome learn this information, they should report this on the corresponding case report form.

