#### Coronary CT protocol

All coronary CTA studies are acquired with a multidetector CT scanner (Discovery HD 750; Gemstone Spectral Imaging, GE Healthcare, Milwaukee, WI, USA). During scanning, participants hold their breath and are still. To obtain better image quality for each contrast agent, scans are performed with different protocols depending on whether high- or low- concentration contrast agents are used. If a high-concentration contrast agent (iopamidol 370 mgI/ml) is used, scans are conducted at 120 kVp for higher BMI (27 < BMI < 35) patients and at 100 kVp for lower BMI (15 < BMI ≤ 27) patients, with adjusted mAs (BMI-based tube potential selection). If a low-concentration contrast agent (iodixanol 270 mgI/ml or iodixanol 320 mgI/ml) is used, scans are conducted 20 kVp lower than in the BMI-based tube potential protocol: that is, at 100 kVp for higher BMI and 80 kVp for lower BMI. A beta-blocker is used for patients with a heart rate higher than 60 beats per minute. Scans initiate a bolus tracking method with a 4.8-s delay after reaching 100 Hounsfield units (HU) in the ascending aorta enhancement.

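### The primary HU comparison is stated as a plain difference of means; adjusting for BMI and site would give a tighter interval at almost no cost

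*Protocol article*

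**What the plan says.** All references are to the protocol article.

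- **Primary statistical analysis.** A 98.33 % confidence interval "for the difference of mean contrast enhancement in the ROIs will be calculated". Noninferiority is concluded "if the lower bound of the two-sided 98.33 % CI lies above the pre-specified noninferiority margin". On the analysis set: "Per-protocol analysis will be performed primarily", with complete cases. No covariate or stratification factor is named for this comparison.
- **Same section, other endpoints.** "Analysis of covariance (ANCOVA) with BMI as a covariate will be used to compare the mean HU of the myocardium on static perfusion CT". The per-vessel and per-segment mixed model is described as "including fixed effects for the group and random intercepts for the patient". Site is in no analysis that the article describes.
- **Randomization.** Patients are allocated "in a 1:1:1 ratio based on each trial site"; Trial design gives eight sites.
- **Coronary CT protocol.** With the 370 mgI/ml agent, tube potential is 120 kVp above BMI 27 and 100 kVp at or below it. With the two lower concentrations, "scans are conducted 20 kVp lower than in the BMI-based tube potential protocol", that is 100 and 80 kVp.
- **Contrast agents.** The injected volume is 80 ml for everyone, whatever the body size.
- **Sample size and power calculation.** The planning SD is 118.93 HU, with no reduction for covariates.

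**The concern.** Each arm's HU distribution mixes two acquisition settings, split at BMI 27, and has a body-size effect on top because the contrast volume is fixed. The article itself says (Background and Discussion) that lower tube potential raises enhancement, so by its own reasoning BMI should predict the primary endpoint. In a plain difference of means, all of that predictable variation stays in the error term. Differences between the eight sites stay there too, although allocation appears to be balanced within site.

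What is at stake is precision. The decision depends on whether the lower confidence limit clears a margin of 51.26 HU, and an interval wider than necessary makes a correct noninferiority conclusion harder to reach.

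**Working it through.** **Inputs.** Margin 51.26 HU, SD 118.93 HU, true difference 0, power 80 %, dropout 10 %, 106 per group (Sample size and power calculation); two-sided 98.33 % interval, which puts 0.00833 in each tail with z = 2.394 (Primary statistical analysis).

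**Step 1: the plan's own figure.** n = 2 × (118.93/51.26)² × (z + 0.842)² = 10.77 × (z + 0.842)².

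- With 0.0167 as a one-sided level (z = 2.128): n = 95, and 95/0.9 rounds up to 106. This matches.
- With the level that the planned interval uses (z = 2.394): n = 113, and 113/0.9 rounds up to 126. This does not match.

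The stated 106 therefore reproduces on the full, unadjusted SD, with 95 evaluable per group.

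**Step 2: the planned interval, unadjusted.**

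- SE = 118.93 × √(2/95) = 17.26 HU
- Half-width = 2.394 × 17.26 = 41.3 HU
- Power = Φ(51.26/17.26 − 2.394) = Φ(0.577) = 71.8 %

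**Step 3: adjustment for BMI.** If BMI explains a share R² of the within-arm variance, the residual SD is 118.93 × √(1 − R²). The documents give no R², so the range is assumed.

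| Assumed R² | Residual SD (HU) | Half-width (HU) | Power at 95 per group | N per group for 80 %, with dropout |
|---|---|---|---|---|
| 0 | 118.93 | 41.31 | 71.8 % | 126 |
| 0.05 | 115.92 | 40.26 | 74.3 % | 120 |
| 0.10 | 112.83 | 39.19 | 77.0 % | 114 |
| 0.20 | 106.37 | 36.95 | 82.3 % | 102 |

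Power at 106 per group would return to 80 % at R² of about 1 − 95/113 = 0.16.

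**Step 4: site, treated separately.** The SD of 118.93 HU is taken from reference 10, which the Discussion calls a single-center study. It therefore contains no between-site variance that adjustment could remove. If between-site variance makes up a share f of the total in this trial (assumed), the unadjusted half-width grows to 41.31/√(1 − f), and adjusting for site brings it back to 41.31. If allocation is stratified by site and site is left out of the analysis, the true one-sided error is 1 − Φ(2.394/√(1 − f)).

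| Assumed f | Half-width, site ignored (HU) | Half-width, site adjusted (HU) | True one-sided error, site ignored (nominal 0.0083) |
|---|---|---|---|
| 0.05 | 42.4 | 41.3 | 0.0070 |
| 0.10 | 43.5 | 41.3 | 0.0058 |
| 0.20 | 46.2 | 41.3 | 0.0037 |

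Ignoring site thus makes the test stricter than intended.

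**The case against.** **The article does not call the analysis unadjusted, and covariates are often left to the SAP.** That is fair: an interval for a difference of means can also come from a covariate model, and sizing on the full SD does not exclude one. But the section does name model terms for other endpoints, BMI among them, and none for the primary one. The natural reading is a plain difference, and the recommendation is worth making whether or not a separate SAP already contains it.

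**An unadjusted difference is valid.** This stands. A reader might infer that the result is biased by BMI, or that the type I error is inflated. The documents support neither. In the full randomised set the difference is unbiased, chance BMI imbalance is part of the sampling error that the interval already covers, and leaving out site errs on the conservative side. The per-protocol, complete-case primary set weakens the protection of randomisation somewhat, but nothing in the article shows that exclusions would depend on BMI.

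**BMI adjustment for the myocardium is not a true inconsistency.** This stands in part. Perfusion CT is done only in patients with more than 50 % stenosis on the randomised scan. That is a post-randomisation subset, where adjustment has its own rationale. The ANCOVA shows that BMI is available and thought relevant to HU; it does not show a contradiction.

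**The low starting power is a different problem.** This also stands. A reader might blame the missing covariates for the 71.8 %, but that figure comes from sizing at a one-sided 0.0167 while planning a two-sided 98.33 % interval. Adjustment may offset part of the shortfall, but did not cause it.

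**Conclusion.** The point holds as an efficiency improvement and not as an error. The primary comparison as written passes over a baseline variable that governs image acquisition, and the factor by which allocation is organised. For BMI, the gain is a half-width 1 to 4 HU smaller and about 2.5 to 10.5 percentage points more power at 95 per group, provided that BMI explains 5 % to 20 % of the variance and that 118.93 HU includes BMI-related variation. Neither condition can be checked from the documents. It would be tempting to credit this gain to BMI and site together; the single-center origin of the SD rules that out. Site adjustment only protects against added between-site variance, and restores the nominal error level if randomisation is stratified by site, which is the most natural reading of the Randomization section.

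**What to change.** Specify the primary estimate for each low-concentration arm as its difference from the 370 mgI/ml arm, with the 98.33 % interval, from a linear model with arm, baseline BMI (continuous, the 27 kg/m² band that sets tube potential, or both) and site. The covariate should be BMI or its band and not the tube potential itself, which differs by arm and is part of what is being compared. Keep the unadjusted difference as a sensitivity analysis. Show the arm difference descriptively in each BMI band, because the bands compare different settings (80 with 100 kVp, and 100 with 120 kVp).

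The cost is wording in the analysis plan, settled before the data are unblinded, and 8 or 9 degrees of freedom (7 for eight sites, 1 or 2 for BMI) out of about 3 × 95 = 285 patients. No new data are needed: eligibility and the choice of tube potential already require BMI, and site is always known.

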### Efficacy analysis

#### Primary efficacy analysis

The primary efficacy measurement is the HU value of the coronary arterial lumen acquired from the comparison of the image quality from the three different protocols of contrast media in coronary CT angiography. The coronary artery is divided into 17 segments according to the modified American Heart Association (AHA) classification, and luminal enhancement is measured for each segment with avoidance of the borderline between the lumen and the vessel wall or epicardial tissue, artifacts, or calcification. Measurement is performed on three different points in each segment and the average value is used for the HU value of each segment. The mean HU value of left main artery and proximal right coronary artery will be compared between the different arms of the trial.

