## Discussion

The CONCENTRATE study is a prospective, multicenter, noninferiority, randomized trial evaluating the enhancement effect of two low-concentration contrast agents compared with the high-concentration contrast agent recommended for sufficient opacification in coronary CT angiography, according to established guidelines [14].

The accuracy of coronary CT angiography in the diagnosis of coronary artery stenosis is affected by image quality, which is dependent on the CNR. To achieve a high CNR, high-concentration contrast agents are usually recommended and have been widely used in everyday clinical practice as a standard protocol [14]. According to a study that compared two contrast agents with different concentrations (400 mgI/ml vs. 320 mgI/ml), coronary arterial enhancement was higher when the high-concentration contrast agent was used and higher enhancement levels were found to be associated with lower numbers of inadequately visualized segments [11]. However, in another study that compared four different concentrations (370, 350, 320, and 270 mgI/ml), image quality grade was higher with low-concentration contrast agents, although high-concentration contrast agents showed greater vascular enhancement [15]. The fact that heart rate variability was lower with low-concentration contrast agents, which were all iso-osmolar agents, whereas the high-concentration contrast agents were all low-osmolar agents, might partially account for the higher image quality obtained with lower-concentration-contrast agents in this study. The lowest enhancement of 369.1 ± 85.4 HU obtained with the lowest concentration of 270 mgI/ml in this study could be considered adequate because adequate intra-arterial enhancement for coronary CT angiography has been considered to require more than 250 HU according to previous reports [13, 14].

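### The mixed model for the secondary per-vessel and per-segment HU analyses lists no vessel or segment effect, so its pooled arm difference is not protected when segments are missing unequally by arm

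*Protocol article*

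**What the plan says.** Under Secondary efficacy analysis the article plans: "Quantitative evaluation of image quality of coronary artery will be performed on a per-vessel and per-segment basis". Under Primary statistical analysis it names the model for repeated observations in a patient: "we will use a linear mixed model, including fixed effects for the group and random intercepts for the patient". The next sentence makes that model the way of handling incomplete patients: "Patients with a missing observation in some vessel or segment will be included in the per-vessel and per-segment analysis by using the linear mixed model".

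The data have many levels per patient. Under Primary efficacy analysis, "The coronary artery is divided into 17 segments according to the modified American Heart Association (AHA) classification", and each segment gets its own HU value. The primary comparison is narrower: "The mean HU value of left main artery and proximal right coronary artery will be compared between the different arms of the trial". It is analysed on complete cases with a 98.33% confidence interval, not with the mixed model.

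The only missingness figure is at participant level and supports the complete-case choice for the primary analysis: "Because missing values are expected for 5 % or fewer of the participants". No segment-level rate is given, overall or by arm, and no HU by segment.

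**The concern.** A patient random intercept absorbs differences between patients. It does not absorb differences between segments. With group as the only fixed effect, segment differences go into the residual, and the model treats a patient's measured segments as exchangeable with the unmeasured ones. If the unmeasured segments tend to have lower HU, the patient's level is overestimated. If this happens more often in one arm, that arm's mean is raised relative to the other.

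So the model is called on to make missing segments harmless, but lacks the term needed to do so. Unequal missingness is plausible here. Measurement has to avoid artifacts and calcification, so some segments may be unmeasurable. The arms differ in both iodine concentration and tube potential. The Discussion also cites a study in which "higher enhancement levels were found to be associated with lower numbers of inadequately visualized segments".

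Separately, the listed terms hold nothing from which a vessel- or segment-specific arm difference could be estimated. At stake is how the secondary per-vessel and per-segment HU results can be read.

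**Working it through.** The plan states no figure on this point, so there is none to reproduce. The check has two parts.

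**1. What the listed terms estimate.** For segment *s* of patient *i*, the stated model is HU(*i,s*) = intercept + β·group(*i*) + patient intercept(*i*) + residual. It has one arm parameter, β. A segment-specific difference needs a segment effect and a group-by-segment term. Neither is named anywhere in the article.

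**2. Size of the bias when the true arm difference is zero.**

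From the article: 17 segments. The simulation below uses 95 patients per arm, close to 106 × 0.9 = 95.4.

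Assumed, not in the documents:
- a linear HU fall of total size G from the first to the last segment;
- only the last 6 segments can be missing, independently of their own HU;
- 10% of these missing in one arm, 20% or 40% in the other;
- for the simulation, between-patient SD 110 and residual SD 45.

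*Closed-form approximation.* With a large patient variance, the group-only model compares arms on roughly the average of patient means. If distal segments are retained with probability r, the expected drop below the first segment is

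drop(r) = (sum over the 11 others + r × sum over the 6 distal) / (11 + 6r).

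For G = 100, segment *s* = 0,…,16 has a drop of 100*s*/16. The 11 others sum to 100 × 55/16 = 343.75. The 6 distal sum to 100 × 81/16 = 506.25.

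- r = 0.9: (343.75 + 455.625)/16.4 = 48.74
- r = 0.8: (343.75 + 405.00)/15.8 = 47.39
- r = 0.6: (343.75 + 303.75)/14.6 = 44.35

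The bias is 48.74 − 47.39 = 1.35 HU for 10% vs 20% missing, and 48.74 − 44.35 = 4.39 HU for 10% vs 40%. It is proportional to G.

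*Simulation.* Sixty datasets per scenario were fitted by generalized least squares with the variance components held fixed, once with group only and once with group plus segment. The table gives the mean difference between the two arm estimates, in HU:

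| Fall G | 10% vs 10% | 10% vs 20% | 10% vs 40% |
|---|---|---|---|
| 0 | 0.00 | 0.00 | −0.01 |
| 50 | 0.03 | 0.75 | 2.29 |
| 100 | −0.01 | 1.40 | 4.60 |
| 150 | 0.09 | 2.01 | 6.96 |

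For G = 100, the simulated 1.40 and 4.60 agree with the closed-form 1.35 and 4.39. The bias vanishes when there is no gradient or when missingness is equal.

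*A second gradient shape.* Take 6 proximal, 5 mid and 6 distal segments with drops of 0, 40 and 100 HU, so drop(r) = (5 × 40 + 600r)/(11 + 6r):

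- r = 0.9: 740/16.4 = 45.12
- r = 0.8: 680/15.8 = 43.04, bias 2.1 HU
- r = 0.7: 620/15.2 = 40.79, bias 4.3 HU
- r = 0.6: 560/14.6 = 38.36, bias 6.8 HU

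Both shapes give about 1 to 7 HU.

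**The case against.** Four objections have weight.

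*The list of terms may be incomplete.* The article writes *including*, and it condenses a fuller protocol. The full model may already contain a segment term. This stands as a reason for low severity. It does not dispose of the point: the article chose to name the terms and named a covariate (BMI) for the myocardial comparison, yet names no segment term for an analysis defined by segments.

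*A per-segment basis may only mean that the segment is the unit of analysis.* The article uses segment basis in that sense for diagnostic accuracy, with a GEE for clustering. On this reading a pooled arm difference is what was planned, and a reader should not infer that the model fails to deliver a promised result. But the pooled difference is the quantity exposed to unequal missingness. Separate fits by vessel would give vessel estimates. Separate fits by segment would give segment estimates, but a patient missing that segment would then drop out, contrary to the stated purpose of the model.

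*The bias is hypothetical.* This stands. The article reports no HU gradient and no segment missingness by arm, and does not mention distal segments. The 20% and 40% rates are assumptions.

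*The direction is open.* This also stands. A reader might infer that the low-concentration arms would lose more segments and so be flattered. The Discussion does cite a study linking higher enhancement to fewer poorly seen segments, but also a four-concentration comparison with better image grades at low concentration. The low-concentration arms are scanned at reduced tube potential, which is expected to maintain enhancement, and the design assumes equal mean HU. Missingness could be equal or reversed.

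A reader might also infer that the bias favours a noninferiority conclusion. The documents do not support that. The noninferiority test compares the left main and proximal right coronary artery outside this model, and the 51.26 HU margin was set for that test.

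**Conclusion.** The point holds in limited form. With the listed terms alone, the secondary model gives one pooled arm difference and no vessel- or segment-level contrast. That difference is biased when mean HU varies by segment and missingness differs by arm.

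The size, about 1 to 7 HU, rests wholly on the assumed gradients and missing rates. It is small beside the planning SD of 118.93 HU. If either condition fails it is zero. It moves the estimate towards the arm with more missing low-HU segments, and which arm that would be is unknown. The primary noninferiority conclusion is unaffected. This is a free improvement of low severity, for secondary analyses only.

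**What to change.** State the model for the per-vessel and per-segment HU analyses with fixed effects for group and for segment (or vessel), and a random intercept for patient. Add the group-by-segment (or group-by-vessel) interaction if vessel- or segment-level contrasts are to be reported. In that case, give the overall arm difference averaged over a fixed set of segments, so that it does not depend on which ones were measured. If the fuller plan already has these terms, naming them is enough.

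The cost is one sentence and one or two model terms, with no new data. In the simulated scenarios the segment effect removes the bias. It would not correct for segments that are unmeasured because their own HU is low, so a table of missing segments by arm would be a useful companion.
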